### Data management

Study data will be collected and managed using REDCap [60] tools hosted at UI. REDCap is a secure, web-based application designed to support data capture for research studies, and it provides (1) an intuitive interface for validated data entry, (2) audit trails for tracking data manipulation and export procedures, (3) automated export procedures for seamless data downloads to common statistical packages, and (4) procedures for importing data from external sources. Study participants will log into REDCap using a secure web-based portal to answer study questionnaires from home. Study staff will use REDCap for manual entry of laboratory and other data and interviewer-administered questionnaires.

### Power and sample size justification

Table 4 displays the mean minimum clinically important difference that can be detected for primary and secondary outcomes to be assessed in the study. The table also includes the SD and correlation between observations over time, with 34 patients in each group after attrition, and an alpha value of 0.05. The minimum differences and SDs are derived from the preliminary studies and peer-reviewed published MS longitudinal studies. Forty-five patients will be recruited in each group, assuming a 25% attrition rate, to attain the 34 patients needed in each group.

**Table 4 Tab4:** Power and sample size justification

Variable	Within Study Groups			Between Study Groups at Last Visit		
	MMCD	SD	Correlation	MMCD	SD Group A	SD Group B
Power is ≥0.85 for the primary outcome						
FSS-9	1.2–2.0	1.1–1.4	0.6	0.7 [35]	0.9	1.1
Power is ≥0.90 for secondary outcomes						
MSQOL-54						
PHC	11.5	16.0	0.6	17.0	17.0	19.0
MHC	12.0	17.0	0.5	18.0	18.0	19.0
6 min walk test	35	50.0	0.5	45.0	45.0	50.0
Timed 25 ft walk	2.9	4.0	0.5	4.0	4.0	4.3
9 hole peg test	5.5	8.0	0.5	8.0	8.1	8.3
PASAT^a^	4.2	6.0	0.5	5.8	6.0	6.3

*Abbreviations: FSS* Fatigue Severity Scale, *MSQOL-54* Multiple Sclerosis Quality of Life 54, *PHC* MSQOL-54 physical health composite score, *MHC* MSQOL-54 mentalhealth composite score, *PASAT* Paced Auditory Serial Addition Test, *MMCD* Minimun Mean Clinical Difference

^a^Power and sample size calculations based on PASAT. Per NMSS, SDMT-O replaces the PASAT measure in this study

### Data analysis

All analyses will be completed by a masked statistician who will not have access to study diet assignment. Data analysis will include both intention-to-treat and per-protocol analytic methods. Data for this study will be analyzed using SAS® 9.4 software (SAS Institute, Cary, NC, USA). Statistical significance will be set at α ≤ 0.05. Descriptive statistics will be calculated for all variables at all data collection times. Outliers will be checked for accuracy and possible entry errors. Respondents who drop out of the study will be compared with those who complete the study so that differences in baseline characteristics that may affect the study results will be detected. Patterns of missing data (missing at random, not missing at random) will be investigated [61]. The analytic methods will account for the type of missing data. The distributions of continuous variables will be evaluated for normality and homogeneity of variance. Appropriate transformations will be applied as needed, and/or statistical analyses for nonnormal data will be performed. Collinearity among fixed effect variables will be examined.

Repeated-measures analyses will use generalized linear mixed models methods to test for within-group and between-group changes in both primary and secondary outcomes. Intraclass correlations for repeated measures within patients will be included in the model structure for analyses. Mixed models for both continuous and categorical outcomes will have both random and fixed effects. Fixed effects will include characteristics such age, sex, intervention group, time indicators, and group-by-time interactions. Intercepts and slopes may be considered as random effects.

## Discussion

Clinical studies of diet in MS are needed because there is uncertainty about the optimal dietary approach to reducing MS-related fatigue. Randomized trials that include assignment to a control or standard care group are the preferred design; however, previous studies including dietary approaches to reduce MS-related symptoms suggest increased participant adherence when a study diet is offered to all participants because dropout is high among nondiet control group participants. Crossover study designs have also been used to test dietary hypotheses. However, we have observed MS symptom reductions among participants following a modified Paleolithic diet and marked increases in MS-related symptoms among those who returned to eating gluten-containing grains or casein-containing dairy products. Therefore, to most effectively and ethically study such dietary approaches, the comparison of two study diets is a better approach than a crossover design for this population.

Maintaining differences between the dietary groups may be challenging because participants may want to modify their eating patterns to make them similar to the diet to which they are not assigned. That is, participants in the low saturated fat diet group may wish to eliminate gluten and dairy, and those in the modified Paleolithic diet group may elect to greatly restrict saturated fat intake. To minimize this, the dietary intervention guide for the low saturated fat diet encourages consumption of gluten-containing grains, and the modified Paleolithic diet encourages consumption of foods containing saturated fat. Additionally, physical symptoms related to consumption of gluten or a reluctance to eat saturated fat are included in the inclusion/exclusion criteria.

Both study groups are likely to experience reductions in MS-related symptoms. Differences within and between groups will be assessed for clinical significance, supported by statistical analyses. Because the primary outcome measure is a self-reported measure and not an objectively measured laboratory or imaging result, the NMSS requested two modifications in the study design. First, a 12-week observation period was added, during which participants continue to eat their usual diet, so that each participant can be her or his own control in the repeated-measures analyses. Second, an accelerometer measure was added to the study to provide an objective assessment of the change in physical activity, sleep duration, and sleep quality.

Given the anecdotal reports regarding improvement in MS symptoms with dietary changes, results from this study will contribute to understanding of the optimal dietary approach for reducing MS-related fatigue. Findings of the study as well as any challenges observed will be submitted to journals for publication. Published papers will be listed on the [name] website ([name]).

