#### Research hypothesis 1a

After 12 weeks of the diet intervention, relative to the observation period, at least 15% of participants in the low saturated fat diet group will demonstrate decreased perceived fatigue (assessed by FSS score), 30% will have improvement in QOL mental health and physical health scores (mean score increase of > 5 points), 50% will demonstrate improved cognition (> 5% improvement in mean Symbol Digit Modalities Test–Oral [SDMT-O] score), and 30% will demonstrate improved motor function (> 5% improvement in mean distance of 6 Minute Walk Test [6MWT]). In the modified Paleolithic diet group, ≥ 60% of the participants will demonstrate decreased perceived fatigue, 70% will have improvement in QOL mental health and physical health score, 70% will demonstrate improved cognition, and 55% will demonstrate improved motor function.

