#### Research hypothesis 1b

After 12 weeks of the diet intervention, participants in the low saturated fat diet group will not have clinically or statistically significant reductions in fatigue or improvements in QOL measures or motor and cognitive function relative to the observation period, whereas participants in the modified Paleolithic diet group will have clinically and statistically significantly reduced fatigue and improved QOL measures and motor and cognitive function as measured by changes in mean scores of the aforementioned measures.

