### Study Design

This 36-week randomized parallel group clinical trial consists of three 12-week periods during which assessments of perceived fatigue, quality of life, motor and cognitive function, physical activity and sleep, diet quality, and social support for eating will be collected. The 12-week periods will consist of:*Observation*: Participants continue eating their usual diet.*Intervention*: Participants will be randomized to either the modified Paleolithic or low saturated fat diet for the intervention period. Participants will receive support by a registered dietitian (RD) through coaching telephone calls and emails.*Follow-up*: Participants will continue the study diet for an additional 12 weeks with minimal RD support to assess the ability of the participant to sustain the study diet on their own.

Study evaluations will be done to compare the effects of the two study diets on perceived fatigue (primary outcome measured by FSS) and secondary outcomes (cognitive function, motor function, QOL). The protocol was prepared according to the Standard Protocol Items: Recommendations for Interventional Trials (SPIRIT) guidelines (*see* Figs. 1 and 2 and Additional file 1: SPIRIT Checklist).

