#### Nutrition counseling

Following randomization, participants will receive two in-person and five phone nutrition counseling sessions with the intervention RD. Personalized emails with feedback will be sent after participants return the diet checklists every 4 weeks. Participants may contact the intervention RD at any time to receive additional support. A final in-person counseling session will be conducted at visit 4. Nutrition counseling will be based on the Self-Determination Theory and use the Motivational Interviewing (MI) communication approach [39–43]. The dietitians providing the intervention will be screened for MI aptitudes prior to being hired, and they will receive training in this area prior to study initiation. The dietitian will also receive ongoing consultative support throughout the study from an RD who is a member of the Motivational Interviewing Network of Trainers (MINT). A lesson plan was developed to guide the counseling session for each in-person study visit. Participants will be asked to consent to being audio recorded during in-person nutrition counseling sessions at visits 2 and 3. The visit 2 audio recordings will be reviewed by the MINT RD to verify fidelity to the study diet guidelines, which consist of explaining the recommended and not recommended foods for the intervention diet and rationale for key dietary components. The MINT RD will review all visit 2 audio recordings and 20% of visit 3 audio recordings using the OnePass instrument [44] to assess use of the MI approach. A mean OnePass score ≥ 4 indicates average competence in MI.

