Participants will view a brief video (< 20 min) that provides background information about the study diet to which they were randomized. Participants will receive an intervention food guide developed by study staff that describes their study diet, as well as *The Multiple Sclerosis Diet Book* [58] (low saturated fat diet) or *The Wahls Protocol* [59] (modified Paleolithic diet), both of which contain sample menus and recipes to assist with meal planning. Additional materials, such as grocery lists, will be provided to assist with diet adoption. A diet checklist that offers guidance to the participant in the form of prompts to eat the foods that are recommended and to avoid those that are not recommended will be provided. The participants and their adult companions will be given a study-adherent meal and practice recording the meal in the diet checklist to facilitate the learning of the principles of the assigned study diet and how to use the daily diet checklist.

Participants will be given a set of diet checklists to complete daily and a 3-day weighed food record booklet as well as an FFQ to complete prior to their next study visit. A self-addressed, stamped envelope will be provided so that participants can return their diet checklists at weeks 16 and 20 for the study dietitian to review. Upon receiving the week 20 checklist, the RD will send an email to acknowledge receipt and provide assessment comments. Participants will be asked to continue their usual physical activity, medication, and stress reduction regimens during the next 24 weeks unless their physician or physical therapist recommends changes.

The study RD will continue to coach the participant via coaching calls 2–3 days after visit 2 and then weekly for 3 weeks. A final coaching call will be made after receipt of the first 4-week diet checklist booklet.

#### Visit 3 – week 24

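### The observation period controls for usual course but not for coaching, expectation or supplements, so within-arm falls in fatigue cannot be attributed to diet

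*Protocol article*

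**What the plan says.** The Discussion gives the reason for the observation period: "Because the primary outcome measure is a self-reported measure and not an objectively measured laboratory or imaging result", the funder asked for two design changes. One was the 12-week period, added "so that each participant can be her or his own control in the repeated-measures analyses". The other was an accelerometer.

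Under Study Design, the content of the observation period is simply "Participants continue eating their usual diet". No counselling is described for it.

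The other elements start at or after visit 2:

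- Coaching: "Following randomization, participants will receive two in-person and five phone nutrition counseling sessions with the intervention RD", with feedback emails (Nutrition counseling).
- Knowledge of the assignment: participants are randomized at visit 2 and watch a video "that provides background information about the study diet to which they were randomized". They also receive a diet book, a food guide and daily checklists (Visit 2 – week 12).
- Family: a relative or companion joins the counselling and is told to be supportive (same section).
- Supplements: both arms start them on day 11 of the diet (text following Table 3).

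Blinding covers the assessors, the medical monitor and the statistician (Study setting; Data analysis). Participants are not listed and must know what they eat.

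Hypotheses 1a and 1b judge each arm against the observation period. Hypothesis 1a sets the share in each arm who "of the participants will demonstrate decreased perceived fatigue" or better on other measures. Hypothesis 1b expects no significant gain in the low saturated fat arm, "whereas participants in the modified Paleolithic diet group will have clinically and statistically significantly reduced fatigue". Hypothesis 3 asks whether these changes last to 24 weeks. Data analysis plans both within-group and between-group tests, and Table 4 has a separate within-group block for FSS.

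**The concern.** A participant serves as their own control only for influences that act equally in both periods. Here the treated period differs from the control period in diet, professional attention, knowledge of the assignment, self-monitoring, family involvement and supplements, all changing at or shortly after one visit. A self-reported fatigue score can respond to any of these.

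The Background gives the purpose as establishing the specific effects of diet. No passage says that coaching, expectation or supplements limit the reading of a within-arm change. A statistically significant fall in an arm could then be reported as the effect of that diet when the design cannot separate it from the rest of the package.

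**Working it through.** **What the observation period can and cannot separate**

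| Source of change in FSS | Present in observation period? | Present after visit 2? | Removed by within-person comparison? |
|---|---|---|---|
| Usual course, drift | yes | yes | yes, if steady |
| Regression to the mean after selection on FSS ≥ 4 | yes | less | partly |
| Dietitian coaching and feedback | none described | yes | no |
| Knowledge of the assigned diet, diet video and book | no | yes | no |
| Study supplements | no | yes, from day 11 | no |
| Diet | no | yes | this is the target |

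The argument rests on this table. The arithmetic below shows only how small a non-diet change needs to be.

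**Inputs** (Power and sample size justification, Table 4): FSS within-group SD 1.1–1.4, correlation 0.6, 34 per group after attrition, alpha 0.05. The protocol does not state sidedness; two-sided is assumed. The calculation takes one before and one after value per participant.

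**The plan's own figures.** 34 / (1 − 0.25) = 45.3, against 45 recruited per group. Within-group power for the smallest listed difference, 1.2, is Φ(1.2/SE − 1.96), with SE as below. It exceeds 0.999 at both SDs, so the stated power of at least 0.85 is met within arms.

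**SD and SE of change**

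- SD of change = SD × √(2 × (1 − 0.6)): 1.1 × √0.8 = 0.984; 1.4 × √0.8 = 1.252.
- SE = SD of change / √34: 0.169 and 0.215.

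**Smallest observed fall that is significant within an arm**

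The critical t on 33 degrees of freedom is about 2.03. Multiplied by the SE, this gives 0.34 points (SD 1.1) and 0.44 points (SD 1.4).

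**Probability of a significant within-arm result when diet has no effect**

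This uses the noncentral t distribution with noncentrality = assumed fall / SE. The protocol gives no size for a non-diet fall, so it is an assumption shown over a range.

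| Assumed true non-diet fall | SD 1.4 | SD 1.1 |
|---|---|---|
| 0 | 0.05 | 0.05 |
| 0.3 | 0.27 | 0.41 |
| 0.5 | 0.62 | 0.82 |
| 0.7 | 0.89 | 0.98 |

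A non-diet shift that is equal in both arms drops out of the between-diet contrast.

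**The case against.** **The Discussion does not claim that bias is removed.** A reader might infer that the protocol presents the observation period as a cure for self-report bias. It says only that participants act as their own controls in repeated-measures analyses, and it names the accelerometer as a second response. This stands, so the sentence needs qualifying rather than retracting. The accelerometer measures activity and sleep, however, and cannot separate coaching from diet for FSS.

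**Hypothesis 1b asks for more than a small p-value.** A reader might infer that a shared non-diet gain would let each diet be declared effective under 1b. The text does not support that, for two reasons.

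- It requires clinical significance too. If Table 4's 1.2 points is the clinical bar, a true non-diet fall of 0.7 gives an observed mean of 1.2 or more with probability only about 0.002–0.01, from (1.2 − 0.7)/SE.
- It predicts no gain in the low saturated fat arm, so a shared gain tends to refute it. With equal gains and independent arms, significance in the modified Paleolithic arm alone has probability p(1 − p), about 0.02–0.24 over the assumed falls of 0.3 to 0.7 points.

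Both stand. The probabilities in the table concern statistical significance only.

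**The 60% target in hypothesis 1a.** With normal changes, a shift of 0.253 × SD of change, or 0.25–0.32 points, gives 60% with some decrease. It is tempting to count this against the observation period. But 1a sets no FSS threshold, so about 50% would show some decrease with no shift at all. The figure mainly reflects the missing threshold.

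**The hypotheses do not name a cause, and the design choice is explained.** Hypotheses 1a, 1b and 3 describe change relative to the observation period, and the overall hypothesis in Aims of study is between diets. The specific effects of diet in the Background are set against an earlier multimodal package. The Discussion concedes that a control or standard-care arm is preferred and cites dropout for not having one. This is fair and limits the severity, but it does not tell the reader how to interpret the planned within-group tests.

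**Expectation and attention are not simply on or off.** Some expectation may exist from consent at visit 1. Coaching calls stop in the follow-up period, so hypothesis 3 looks at persistence with less attention. Neither makes the change from observation to week 24 specific to diet.

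**Conclusion.** The concern holds for the within-arm claims: hypotheses 1a and 1b, and 3 in so far as it builds on them. The observation period is useful against drift and part of the regression to the mean. It does not control for influences that begin at or after visit 2 alongside the diet.

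On Table 4's inputs, within-arm statistical significance needs an observed fall of only about 0.34–0.44 FSS points, against a listed within-group clinical difference of 1.2–2.0. An assumed non-diet fall of 0.5 would reach significance in an arm with probability 0.62–0.82. These figures assume a two-sided test, 34 completers per arm and single before and after scores.

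A reader might go further in either direction: that the randomized comparison is equally compromised, or that it is wholly clean. Neither follows. The coaching schedule and supplement regimen are common to both arms, so those elements do not by themselves undermine hypotheses 2a and 2c. Expectation need not be equal, because participants are unblinded and receive different diet-specific books and videos.

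**What to change.** 1. In the Discussion, qualify the own-control sentence: the observation period accounts for usual-course change and part of the regression to the mean, but not for coaching, expectation or supplements, which begin at or after visit 2.
2. State that diet-specific conclusions on FSS and the other self-reported outcomes rest on the randomized between-diet contrasts (2a and 2c). Add that coaching schedule and supplements are common to both arms, but expectation may differ between them.
3. Label the within-arm results under 1a, 1b and 3 as descriptive changes under the whole package of diet, coaching, supplements and expectation.

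This costs wording only, with no new participants, visits or measurements. The downside is that the trial gives up a stand-alone efficacy claim for either diet.

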### Trial status

Recruitment commenced August 24, 2016. We have consented 58 participants to date.

## Abbreviations

6MWT: 6-Minute walk test
9HPT: 9-Hole Pegboard Test
ADA: American Diabetes Association
BMI: Body mass index
Cardio IQ®: Omega-3 (EPA + DHA) index, omega-6/omega-3 ratio, EPA/arachidonic acid ratio, arachidonic acid, EPA, and DHA
DHA: Docosahexaenoic acid
DSMB: Data and Safety Monitoring Board
EPA: Eicosapentaenoic acid
FFQ: Food Frequency Questionnaire
FSMCF: Fatigue Scale for Motor and Cognitive Function
FSS: Fatigue Severity Scale
HADS: Hospital Anxiety and Depression Scale
HDL: High-density lipoprotein
IPAQ-L: International Physical Activity Questionnaire–Long
IRB: Institutional review board
MFIS: Modified Fatigue Impact Scale
MHI: Mental Health Inventory
MI: Motivational Interviewing
MINT: Motivational Interviewing Network of Trainers
MRI: Magnetic resonance imaging
MS: Multiple sclerosis
MSIS v2: Multiple Sclerosis Impact Scale version 2
MSQ: Medical Symptoms Questionnaire
MSQOL54: Multiple Sclerosis Quality of Life 54
NMSS: National Multiple Sclerosis Society
PDQ: Perceived Deficits Questionnaire
PSQI: Pittsburgh Sleep Quality Index
PSS 10: Perceived Stress Scale 10
QOL: Quality of life
RD: Registered dietitian
REDCap: Research Electronic Data Capture
RRMS: Relapsing-remitting multiple sclerosis
SDMT-O: Symbol Digit Modalities Test–Oral
SF36: 36-Item Short Form Health Survey
SPMSQ: Short Portable Mental Status Questionnaire
T25FW: Timed 25-foot walk
UI: University of Iowa
